### Statistical procedures

#### Feasibility and qualitative analyzes

Descriptive statistics will be used to summarize feasibility outcomes. Qualitative data are included to permit a deeper understanding of quantitative findings in this new population. A research assistant supervised by study investigator will use content analysis and constant comparison to identify, expand or merge themes in transcripts of recorded interviews, and develop a codebook of themes and exemplar quotes. We will tabulate themes by sex and within groups by sampling characteristics. This will identify common views about Education and Self-Management Strategies group design and its impact, yielding insight on how to further refine the intervention. By virtual meeting, the Research Team will interpret findings, which we will use to refine intervention design prior to the ensuing Phase 2 RCT.

#### Efficacy analyzes

To assess pre-to post-treatment and follow-up changes for the primary outcome (PMCSMS), we will undertake repeated measures group (Education vs. Mindfulness) by time (pre-, post-, and follow-up-education/mindfulness/waitlist group). ANCOVAs controlling for acute COVID-19 severity and time post-diagnosis. Secondary outcomes will also be examined in the same manner.

Hierarchical regression analyzes will be performed to examine impact of potential moderator variables on pre-to-post treatment improvement on the PMCSMS. In the first block, the moderators will be age, acute COVID severity, and time-post diagnosis. Sex and gender will be included in the second block, and Brief COPE, AIIR and MHLC will be added in the final block. Analyzes of repeated measures data will be performed using the Mixed Models for Repeated Measures (MMRM) methodology (96). We will employ a comparison of bias-corrected covariance estimators for MMRM analysis in longitudinal data with dropouts in order to accommodate the possibility of missing assessments or of assessments at different times post-diagnoses and to provide an effective framework for hierarchical regression analyzes and further exploratory analyzes (96).

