#### Efficacy measures (Objective 2)

All primary and secondary outcomes are PROMs. Table 3 summarizes the timeline of the outcome measure collection.

(i)Primary outcome:

Perceived Medical Condition Self-Management Scale (85) (PMCSMS). An 8 item tool using a 6-point scale to measure confidence to self-manage symptoms, with strong validity and reliability (85, 86), and associated with high treatment adherence and beneficial outcomes (85).

(ii)Secondary outcomes:

Utilization of Healthcare Services Questionnaire. This tool was created by our group to measure past and planned healthcare-related visits.Depression, Anxiety and Stress Scale (DASS-21 (87)). A 21-item tool that uses a 4-point scale to measure stress, depression and anxiety symptoms.Quality of Life Enjoyment and Satisfaction Questionnaire – Short Form (Q-LES-Q-SF (88)). A 16-time tool that uses a 5-point scale to measure quality of life and degree of enjoyment and satisfaction experienced by participants in various areas of daily living.Adapted Illness Intrusiveness Rating (AIIR (89, 90)). A 13-item scale using a 7-point scale to measure intrusiveness of symptoms in daily life.Life Orientation Test – Revised (LOT-R) (91). A 10-item tool using a 5-point scale to measure dispositional optimism.International Physical Activity Questionnaire (IPAC) (92). An 8-item tool to measure engagement in physical activity.

(iii)Control/Moderator variables

Brief COPE (93). A 28-item tool using a 4-point scale to measure ways of coping with stress in life.Somatic Symptom Scale – 8 (SSS-8 (94)). An 8-item tool using a 5-point scale to measure of somatic symptom burden.Multi-dimensional Health-Related Locus of Control (MHLC (95)). An 18-item tool to measure the locus of control for health-related behaviors.

**Table 3 tab3:** Summary and timeline of outcome measure collection.

Timeline		Outcome category	Outcome measures
Pre-intervention	Week 0; prior to first session	Feasibility (Objective 1)	Recruitment rate
		Efficacy (Objective 2)	Perceived Medical Condition Self-Management Scale Utilization of Healthcare Services Questionnaire Depression, Anxiety and Stress Scale Quality of Life Enjoyment and Satisfaction Questionnaire – Short Form Adapted Illness Intrusiveness Rating Brief COPE and Life Orientation test Somatic Symptom Scale Multi-dimensional Health-Related Locus of Control International Physical Activity Questionnaire

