Intervention	Weeks 1–8	Feasibility (Objective 1)	Retention/adherence rate, Session Feedback Form
Post-intervention	Week 8; last session	Feasibility (Objective 1)	Qualitative exit interview (Education intervention group only)
		Efficacy (Objective 2)	(all efficacy outcomes mentioned above)
1-month follow-up (phase 1 and phase 2)	Week 12	Efficacy (Objective 2)	(all efficacy outcomes mentioned above)
3-month follow-up (phase 2 only)	Week 20	Efficacy (Objective 2)	(all efficacy outcomes mentioned above)

This table describes all the outcome measures and their timeline for administration. COPE: Coping Orientation to Problems Experienced Inventory.

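### The primary PMCSMS model treats the pre-treatment score as a time level instead of adjusting for it, which gives up precision that costs nothing to recover

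*Protocol article*

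**What the plan says.** The article's model for efficacy is set out under Statistical procedures, Efficacy analyzes. For the PMCSMS, "we will undertake repeated measures group (Education vs. Mindfulness) by time (pre-, post-, and follow-up-education/mindfulness/waitlist group"), so the score before treatment is an outcome at the first of three time levels. The model is then labelled "ANCOVAs controlling for acute COVID-19 severity and time post-diagnosis". Those two variables are the only covariates listed, and the secondary outcomes are to be handled in the same way.

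The following paragraph, which also covers the moderator regressions, adds: "Analyzes of repeated measures data will be performed using the Mixed Models for Repeated Measures (MMRM) methodology". It gives missing assessments and irregular assessment times as the reason, and continues: "We will employ a comparison of bias-corrected covariance estimators for MMRM analysis in longitudinal data with dropouts".

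Under Efficacy measures, the PMCSMS is described as "An 8 item tool using a 6-point scale to measure confidence to self-manage symptoms", with no visit attached to it as primary. Table 3 has it collected at week 0, at week 8 and at week 12, the last being the "1-month follow-up (phase 1 and phase 2") assessment. The baseline score is therefore collected before the first session by design.

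**The concern.** When baseline is a level of time and each arm has its own baseline mean, the treatment effect lies in the group-by-time interaction. For any one follow-up visit, that is the difference between arms in mean change from baseline. Subtracting the whole baseline score fixes its coefficient at 1, whereas regression on baseline uses the coefficient the data support, which is rho when the variances are equal. The first choice carries extra noise whenever rho is below 1.

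The two covariates listed do not make up for this. Both are fixed for a participant, so unless they are also interacted with time they cancel out of within-person change.

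What is at stake is the precision of the Phase 1 effect estimate. The Aims and hypotheses section gives Phase 1 the task of determining feasibility and effect size and bases the Phase 2 power analysis on its results. The Ethics and dissemination section makes the larger trial depend on seeing early signs of efficacy. A noisier estimate makes both steps less reliable.

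**Working it through.** **Inputs from the article.** Time levels and covariates: Efficacy analyzes. Sample size (Participants): effect size 0.59, 26 pairs, 20% attrition, a further 25% for the 1-month follow-up, 45 per arm. Visits: Table 3.

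**Assumptions, because the article gives no figure.** Equal variance at each visit (SD = 1). Correlation rho between baseline PMCSMS and a follow-up visit, read as the correlation after the other covariates, from 0.3 to 0.8. For power only, a true arm difference of 0.5 SD, two-sided alpha 0.05.

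**Step 1: the plan's own figure.** A paired t-test at d = 0.59, two-sided alpha 0.05 and power 0.80 needs 25 pairs; at 26 pairs the power is 0.824. Inflation: 26/0.80 = 32.5, so 33; 33/0.75 = 44, against 45 stated. The figure reproduces to within one. It sizes a within-person comparison, so it says nothing about the precision of the comparison between arms. Expected numbers per arm: 45 × 0.80 = 36 at week 8 and 36 × 0.75 = 27 at week 12.

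**Step 2: variance of the arm contrast at one visit, same participants in both analyses.**
- Baseline as a time level, free arm means: proportional to Var(Y_t − Y_0) = 2(1−rho).
- Baseline as a covariate: proportional to 1−rho².
- Ratio: (1−rho²)/[2(1−rho)] = (1+rho)/2.
- Extra participants needed by change scores: 2/(1+rho) − 1 = (1−rho)/(1+rho).

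| rho | 2(1−rho) | 1−rho² | ratio | extra n |
|---|---|---|---|---|
| 0.3 | 1.40 | 0.91 | 0.65 | 54% |
| 0.5 | 1.00 | 0.75 | 0.75 | 33% |
| 0.6 | 0.80 | 0.64 | 0.80 | 25% |
| 0.7 | 0.60 | 0.51 | 0.85 | 18% |
| 0.8 | 0.40 | 0.36 | 0.90 | 11% |

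**Step 3: effect on power** (noncentral two-sample t, 0.5 SD difference, participants seen at the visit; change score → baseline-adjusted).

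| rho | 36 per arm | 27 per arm |
|---|---|---|
| 0.5 | 0.55 → 0.68 | 0.44 → 0.55 |
| 0.6 | 0.65 → 0.74 | 0.52 → 0.62 |
| 0.7 | 0.77 → 0.83 | 0.64 → 0.71 |

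The difference detectable with 80% power at 36 per arm falls from 0.67 to 0.58 SD at rho 0.5, and from 0.52 to 0.48 SD at rho 0.7.

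**Step 4: allowance for MMRM with dropout.** With baseline as an outcome level, MMRM also uses participants who have only a baseline. If a fraction f of N is seen at the visit and loss is at random, the variance for the time-level model is (1−rho²)/(fN) + (1−rho)²/N, against (1−rho²)/(fN) with baseline as covariate. The excess is f(1−rho)/(1+rho). With f = 0.80 this is 0.8 × 0.333 = 27%, 0.8 × 0.25 = 20% and 0.8 × 0.176 = 14% at rho 0.5, 0.6 and 0.7. The gain in Step 3 is therefore slightly overstated for an MMRM under the full planned loss, but it does not disappear.

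**The case against.** The best defence is that baseline as a time level is a legitimate and unbiased analysis of a randomised trial. That stands: the point is about efficiency only. The size of the loss depends on a correlation the article does not give, shrinks as that correlation rises (10% of the variance at rho 0.8), and vanishes if the MMRM gives both arms a common baseline mean. The article neither states nor excludes such a constraint. Phase 1 is also mainly a feasibility phase, and no confirmatory p-value is claimed for it. This lowers the stakes, but the estimate is still used for Phase 2.

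Three stronger readings are tempting, and the article does not support them.

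- A reader might infer that repeated-measures ANCOVA and MMRM are rival primary analyses that would analyse different people. But the section assigns repeated-measures data to MMRM and gives missing assessments as the reason. The plain reading is one group-by-time model fitted by MMRM, not a complete-case analysis.
- A reader might infer that comparing covariance estimators inflates the error rate. The article does not say that several standard errors will be computed and one picked, the phrase is tied to a cited source not at hand, and no calculation here measures such an effect. Choice of estimator is ordinary content for an analysis plan.
- A reader might infer that the test has no direction. The hypotheses state one: more confidence to self-manage with education than with mindfulness.

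The absence of a named primary visit or contrast may likewise be settled in an analysis plan that is not shown, so it is no separate finding.

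**Conclusion.** The point holds as a loss of efficiency, not of validity. As written, the article spends the baseline PMCSMS as an outcome level and leaves it out of the covariates. With the same participants in both analyses, conditioning on it would multiply the variance of the arm difference by 0.75 to 0.85 at rho 0.5 to 0.7. Leaving it out is equivalent to needing 33% to 18% more participants, or 27% to 14% under MMRM with the planned 20% loss. These sizes rest on the assumed correlations, equal variances across visits, free baseline means in each arm and, for the dropout version, loss at random. The change is well worth making, but the trial would not be invalid without it.

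**What to change.** Replace the group-by-time ANCOVA sentence with one model: the MMRM already planned, fitted to PMCSMS at weeks 8 and 12, with arm, visit, arm-by-visit, baseline PMCSMS, baseline-by-visit, acute COVID-19 severity and time since diagnosis. An equivalent alternative is to keep all three time levels and constrain the arms to a common baseline mean. Use the same baseline adjustment for the continuous secondary outcomes.

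While rewording, three clarifications are cheap: say that the MMRM is the model and drop the ANCOVA label; name one arm contrast at one visit as primary (week 8 would match the pre-to-post change already used in the moderator analysis); and label any comparison of covariance estimators as a sensitivity analysis.

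The cost is analysis wording only. The baseline score is already collected at week 0, and no visit, questionnaire or participant is added.

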We will undertake a two-phase randomized controlled trial (RCT) to determine feasibility and effect size (Phase 1) and efficacy (Phase 2) for a novel 8-week Education and Self-Management Strategies group compared to a mindfulness skills program. Phase 2 is a full-scale quantitative-only RCT, with refinements and power analysis based on Phase 1 results, and an additional third no-treatment control arm. Outcomes of interest include confidence and ability to self-manage symptoms, quality of life, healthcare utilization. Hypotheses: Both interventions will be associated with enhanced mood, anxiety, quality of life and management of dyspnea symptoms. The education and self-management strategies program will additionally increase confidence to self-manage symptoms, decrease intrusiveness of Long-COVID symptoms in everyday life, and decrease medical visits, more so than the mindfulness group.

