## Methods

### Participants

Individuals (*N* = 90; >18 years) with previously diagnosed COVID-19 and experiencing symptoms lasting for more than 3 months (i.e., persisting symptoms) are currently being recruited for Phase 1. Sample size is based on paired tests from our prior concussion study (79) (*N* = 61; under review) that used the same primary outcome. With effect size 0.59 and standard alpha and beta values, 26 pairs are needed. Factoring (i) 20% attrition (conservative given 7% attrition in a similar concussion study [79; under review] and 9% in the pilot group for the present study), and (ii) a further 25% for 1-month follow-up, we will recruit N = 45 for education of self-management strategies group and N = 45 for mindfulness skills group. Key inclusion criteria are: positive COVID-19 diagnosis a minimum of 3 months prior to study participation; proof of COVID-19 diagnosis through PCR, rapid antigen or serology test; self-report experiencing 3 or more persisting symptoms from 2 or more categories of mood, cognitive and somatic domains; age > 18; and English speaking. Key exclusion criteria include past acute ventilator support; past or present major neurological/psychiatric conditions including dementia, mild cognitive impairment, psychotic illness, mania, chronic fatigue syndrome, fibromyalgia, chronic Lyme disease, and/or traumatic brain injury.

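### As written, the primary PMCSMS model uses the week-0 score only as an outcome level, so the Education-versus-Mindfulness contrast is unbiased but less precise than the collected data allow

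*Protocol article*

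**What the plan says.** All references are to the protocol article.

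- **Model terms** (Efficacy analyzes): "we will undertake repeated measures group (Education vs. Mindfulness) by time (pre-, post-, and follow-up-education/mindfulness/waitlist group"). The pre-treatment score is thus a level of the time factor, alongside post-treatment and follow-up.
- **Covariates** (same section): "ANCOVAs controlling for acute COVID-19 severity and time post-diagnosis". Baseline PMCSMS is not listed, and nothing states that the arms share a baseline mean.
- **Estimation** (same section): "Analyzes of repeated measures data will be performed using the Mixed Models for Repeated Measures (MMRM) methodology". The text that follows concerns missing or off-schedule assessments and covariance estimators. It does not say how baseline is handled.
- **Secondary outcomes** (same section): "Secondary outcomes will also be examined in the same manner".
- **Baseline availability** (Table 3): PMCSMS is collected at "Week 0; prior to first session".
- **Hypothesis** (Aims and hypotheses): the Education programme is expected to do better than Mindfulness on confidence to self-manage, intrusiveness and visits; the sentence ends "decrease medical visits, more so than the mindfulness group". The question that decides the trial is therefore between arms.

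**The concern.** Allocation is randomised 1:1, so the true difference between arms at week 0 is zero. A model that gives each arm its own week-0 mean estimates that zero from the data and subtracts the estimate, with its noise, from the later difference. Adjusting for the baseline score, or imposing a common baseline mean, avoids this.

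What is at stake is precision. The between-arm interval is wider than the same patients could give. The same model serves every secondary scale. Phase 1 is also meant to supply the effect size on which the Phase 2 power analysis rests, so avoidable noise is carried forward. The Phase 1 sample size was set on paired, within-group tests, so the between-arm contrast has no stated power of its own and little precision to spare.

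**Working it through.** **1. The plan's own figure.** The Participants section states: "With effect size 0.59 and standard alpha and beta values, 26 pairs are needed". Taking the standard values as two-sided 0.05 and 80% power (an assumption), a paired t-test at 0.59 needs 24.5, so 25 pairs (power 80.8%); 26 pairs give 82.4%. Inflating for the stated losses: 26/0.80 = 32.5, so 33; 33/0.75 = 44, against 45 per arm stated. The figure reproduces to within a patient or so. It rests on a within-group test, so nothing below changes it.

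**2. Variance of the between-arm contrast.** Assume complete data, equal variance σ² at each visit, n per arm and pre-post correlation r.

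- Free baseline means (the model as written): the week-8 minus week-0 group contrast has variance (2σ²/n) × 2(1−r).
- Baseline as covariate, or common baseline mean: (2σ²/n) × (1−r²).
- Ratio: (1−r²) / [2(1−r)] = (1+r)/2, which is below 1 for every r below 1.

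The direction of the loss therefore does not depend on r. Only its size does.

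**3. Numbers.** r is not in the documents, so a range is shown. For power, take 36 per arm at week 8 (45 × 0.80) and an illustrative between-arm difference of 0.5 SD, which is also an assumption (two-sided 0.05, t-test).

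| r | 2(1−r) | 1−r² | Ratio | Planned interval wider by | Power, as written | Power, baseline-adjusted |
|---|---|---|---|---|---|---|
| 0.4 | 1.20 | 0.84 | 0.70 | 19.5% | 0.48 | 0.63 |
| 0.5 | 1.00 | 0.75 | 0.75 | 15.5% | 0.55 | 0.68 |
| 0.6 | 0.80 | 0.64 | 0.80 | 11.8% | 0.65 | 0.74 |
| 0.7 | 0.60 | 0.51 | 0.85 | 8.5% | 0.77 | 0.83 |
| 0.8 | 0.40 | 0.36 | 0.90 | 5.4% | 0.91 | 0.94 |
| 0.9 | 0.20 | 0.19 | 0.95 | 2.6% | 0.997 | 0.998 |

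**4. With the plan's attrition.** A three-visit model with unstructured covariance was simulated with 45, then 36, then 27 per arm (20% loss, then a further 25%), 200 trials for each r. The variance ratios for common against free baseline were 0.73, 0.79, 0.83 and 0.87 at r = 0.4, 0.5, 0.6 and 0.7, close to the closed form. The corresponding standard errors are about 7% to 15% smaller (√0.87 = 0.93; √0.73 = 0.85).

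**5. Do the two named covariates make up for it?** In one simulated complete dataset of 90, the week-8 contrast was 0.1309 (SE 0.1790) both without and with a time-constant covariate entered as a main effect. It changed only when covariate-by-visit terms were added. With 45/36/27 per arm and a covariate correlated 0.5 with the outcome, the main effect shifted the estimate by up to about 0.08 SD at r = 0.4 and 0.05 SD at r = 0.7, but the gain in precision was negligible.

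**The case against.** **The covariates may do some work.** A reader might infer that adjusting for severity and time post-diagnosis is empty, because person-level constants cancel from a within-person change. The document does not support that. It does not say that the covariates enter as main effects only, and the classical repeated-measures ANCOVA lets each covariate act differently at each time. Exact cancellation also needs complete data, while the plan expects losses. Time post-diagnosis may even be recorded per assessment, since the section allows for assessments at differing times after diagnosis. What stands is narrower: these covariates are not a substitute for the baseline score, and as time-constant main effects they add almost no precision to this contrast.

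**An unseen analysis plan may handle baseline properly.** Listing the pre-treatment score as a time level is compatible with a common-mean constraint, and an article condenses. This is fair, and it limits how firmly one can say what will be run. But the article does name its time levels and its covariates, and the model so described does not adjust for baseline.

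**Within-arm change is a stated aim.** The section sets out to assess change from pre-treatment, and improvement is hypothesised in both arms. Dropping week 0 as an outcome would lose direct estimates of that change. This stands, and it decides which fix is preferred.

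**The gain could be small.** The scale is described as reliable, so r may be high. At 0.8 to 0.9 the variance saving is only 5% to 10%. This also stands.

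**Conclusion.** The point holds as one of efficiency. As published, the Education-versus-Mindfulness contrast is in essence a difference in change scores, although a week-0 score that would sharpen it is already collected. Baseline adjustment would multiply its variance by (1+r)/2: 0.70 to 0.85 for r of 0.4 to 0.7, and 0.90 to 0.95 for r of 0.8 to 0.9. These figures rest on an assumed r, equal variances across visits and, in closed form, complete data; the simulation with the planned losses agrees closely for r of 0.4 to 0.7. The power figures rest further on an assumed 0.5 SD difference.

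A reader might go on to infer that the planned comparison is biased or invalid. It is not: under randomisation the change-score contrast is unbiased. Nor are the 26 pairs or the 45 per arm affected. The change is worth making because it is free and because the same model serves the secondary scales and informs Phase 2.

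**What to change.** In Efficacy analyzes, keep the three-visit mixed model, state that the two arms are constrained to a common week-0 mean, and enter acute severity and time post-diagnosis with covariate-by-visit terms. This is the preferred form because it retains the within-arm change estimates that the protocol wants.

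Alternatively, for the between-arm contrast, model the week-8 and week-12 scores with group, visit and group-by-visit as factors, and baseline PMCSMS, baseline-by-visit and the two named covariates as covariates. Within-arm change would then have to be estimated separately.

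Apply the same approach to each secondary scale with its own week-0 score. If an analysis plan already does this, align the article's wording with it.

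Cost: analysis wording only. No new data, visits or participants are needed.

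### The moderator regression lists only main effects, so as written it cannot separate variables that change the Education-versus-Mindfulness difference from variables that predict improvement in either arm

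*Protocol article*

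**What the plan says.** In the protocol article, the Efficacy analyzes section gives the aim of the regression: "Hierarchical regression analyzes will be performed to examine impact of potential moderator variables on pre-to-post treatment improvement on the PMCSMS". It then assigns variables to blocks: "In the first block, the moderators will be age, acute COVID severity, and time-post diagnosis", followed by "Sex and gender will be included in the second block, and Brief COPE, AIIR and MHLC will be added in the final block".

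Treatment arm appears in that section only in the separate repeated-measures analysis: "we will undertake repeated measures group (Education vs. Mindfulness) by time". One later sentence connects the two by saying that MMRM is used, among other reasons, "to provide an effective framework for hierarchical regression analyzes and further exploratory analyzes".

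The Efficacy measures section sorts the instruments differently. Brief COPE, SSS-8 and MHLC stand under Control/Moderator variables. SSS-8 is described there as "An 8-item tool using a 5-point scale to measure of somatic symptom burden". AIIR stands under Secondary outcomes: "Adapted Illness Intrusiveness Rating (AIIR (89, 90)). A 13-item scale using a 7-point scale to measure intrusiveness of symptoms in daily life". Table 3 collects all of these at week 0, week 8 and week 12.

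**The concern.** In a two-arm trial, a moderator of treatment effect is a variable across whose levels the difference between the arms changes. That requires arm and its product with the variable in the model. The blocks listed here contain neither, yet the variables in them are called moderators. A significant coefficient would show that a variable goes with more or less improvement, which may be equally true in both arms.

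Two smaller points follow. The outcome is a pre-to-post change and baseline PMCSMS is in no block, so a variable related to starting confidence can appear to predict improvement through regression to the mean. The variable list also does not match the Efficacy measures section: SSS-8 is in no block, while AIIR, a secondary outcome that the Aims and hypotheses section expects Education to lower more than Mindfulness does, is in the final block with no statement of which measurement is used.

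At stake is the reading of a secondary analysis. A general predictor could be reported as identifying who does better with one programme than the other, and a real moderator could be missed.

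**Working it through.** **Stated figures.** The plan gives no figure for this regression. Its sample size is for paired tests and is not in dispute: 26 pairs, then 26/0.80 = 32.5, rounded to 33, and 33/0.75 = 44, against 45 per arm stated. The number available for a pre-to-post analysis after the stated 20% attrition is 90 × 0.80 = 72, or 36 per arm.

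**Terms in the model.**

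| Block | Variables | Arm | Arm × variable | Baseline PMCSMS |
|---|---|---|---|---|
| First | age, acute severity, time since diagnosis | no | no | no |
| Second | sex, gender | no | no | no |
| Final | Brief COPE, AIIR, MHLC | no | no | no |

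**What such a model estimates.** Let a variable have slope b₁ on improvement in one arm and b₂ in the other. With 1:1 allocation and no arm term, its coefficient estimates about (b₁ + b₂)/2. Moderation is b₁ − b₂. If b₁ = b₂ ≠ 0, there is no moderation but the variable tends to be flagged. If b₁ = −b₂, there is strong moderation but the coefficient is near zero.

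**How often a purely prognostic variable is flagged (single-variable test).** The correlation r with improvement is an assumption, since the documents give none. With two-sided alpha 0.05 and n = 72, the probability is Φ(atanh(r) × √(n − 3) − 1.96), where √69 = 8.307.

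| Assumed r | atanh(r) × 8.307 | Probability flagged |
|---|---|---|
| 0.2 | 0.2027 × 8.307 = 1.68 | Φ(−0.28) = 0.39 |
| 0.3 | 0.3095 × 8.307 = 2.57 | Φ(0.61) = 0.73 |
| 0.4 | 0.4236 × 8.307 = 3.52 | Φ(1.56) = 0.94 |

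**Check with several covariates.** A simulation used 5,000 trials per setting, eight independent standardised covariates, residual SD 1 and arm effect 0.3 (all assumed). The model as written was compared with one that adds arm and the arm-by-variable term.

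| N | Prognostic only (slope 0.4 in both arms): as written | Same: interaction test | Crossover (+0.4 / −0.4): as written | Same: interaction test |
|---|---|---|---|---|
| 54 | 74% | 4.5% | 6.8% | 72% |
| 72 | 87% | 5.0% | 6.3% | 85% |
| 90 | 94% | 5.3% | 6.3% | 93% |

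The 87% at N = 72 is below the 94% above partly because slope 0.4 here means a correlation of 0.4/√(1 + 0.16 + 0.0225) = 0.37, and partly because seven other covariates are fitted.

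**Precision of a proper interaction.** For an evenly split binary moderator, 72 patients form four cells of 18. The standard error of the interaction is √(4/18) = 0.47 SD. With the t quantile on 68 degrees of freedom (about 1.995), the 95% interval is about ±0.94 SD.

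**Change score without baseline.** Suppose PMCSMS has equal variance before and after, with correlation ρ between them, and a variable correlates c with baseline and relates to the post score only through baseline. Its correlation with change is then c(ρ − 1)/√(2(1 − ρ)) = −c√((1 − ρ)/2), which is not zero unless c = 0 or ρ = 1. If the variable relates equally to both scores, the correlation is zero. The artefact is therefore possible, not certain.

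**The case against.** The strongest reply is that a journal article condenses. The section allocates variables to blocks and writes no model equation. The repeated-measures design is group by time, and MMRM is offered as a framework for the regression, so arm may be in the underlying model. This stands in part: the text does not exclude arm. But it runs from the first block to the final one and calls the listed variables moderators, and the MMRM sentence adds no term. A model that is spelled out and does not answer its own question is more than missing detail. Fitting it separately by arm is not stated and would still give no test of a difference between arms.

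Four stronger readings are tempting, and the documents do not support them.

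- *The model can never detect moderation.* This is exact only for a crossover. Where slopes differ but do not average to zero, the variable may be flagged; the model just cannot tell that from prognosis.
- *SSS-8 was wrongly left out and AIIR wrongly put in.* The heading is Control/Moderator, so SSS-8 may be meant as a control. AIIR is measured at week 0, and a baseline value can be a legitimate moderator of a trial in which the later value is an outcome. What remains is a mismatch between lists and an unstated time point.
- *Phase 2 would target patients on this result.* The article bases Phase 2 refinements on Phase 1 results in general and ties refinement of the intervention to the qualitative findings. Nothing ties it to this regression.
- *A false flag is near certain.* The 94% needs r = 0.4; at r = 0.2 the figure is 39%.

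It is also fair that a proper interaction would be imprecise: ±0.94 SD is wide beside the planning effect of 0.59. That is a reason to call the result exploratory, not to test a different quantity under the same name.

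**Conclusion.** The point holds in this form: the regression as written does not distinguish effect modification from general prediction of improvement, and it would find a crossover moderator at little more than the 5% error rate (6–7% in simulation). A purely prognostic variable would be labelled a moderator in about 39% to 94% of trials for assumed correlations of 0.2 to 0.4 at n = 72, against about 5% for an interaction test. The percentages rest on those assumed effects; the direction does not.

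The mismatch over SSS-8 and AIIR is real but is a matter of clarification. This is a secondary analysis: neither the Education-versus-Mindfulness comparison on PMCSMS nor the sample size changes.

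**What to change.** Choose one of two courses and say which.

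1. **Test moderation.** Model week-8 PMCSMS on arm and baseline PMCSMS. Keep the block structure if it is wanted, but enter each candidate with its arm-by-variable term, using baseline values only. Report each interaction with its 95% confidence interval and label the whole analysis exploratory.
2. **Keep main effects only.** Rename the analysis as one of predictors of improvement, drop the word moderator, and preferably still adjust for arm and baseline PMCSMS.

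In either case, make the Efficacy measures and Efficacy analyzes sections agree. State whether SSS-8 is a control or a moderator and enter it accordingly. If AIIR is kept, state that its week-0 value is used, and say the same for Brief COPE and MHLC, which Table 3 also repeats after treatment.

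The cost is wording: every variable is already collected. The downside of the first course is wide intervals (about ±0.94 SD for an evenly split binary moderator at n = 72) and several tests. With the eight variables listed and 5% each, 8 × 0.05 = 0.4 false flags are expected if none is a moderator.
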